### Data management

The local investigators at USZ, REHAB, INSEL and EME-OTs will be carefully trained by the principal investigator in their research-relevant tasks. All data collected on paper are entered into Redcap by the local investigator and regularly checked for accuracy by the principal investigator. Project data will be handled with the uttermost discretion and is only accessible to authorised personnel who require the data to fulfil their duties within the scope of the research project. On the case report forms and other project-specific documents, participants are only identified by a unique participant number. At the end of this project, we will remove any direct identifiers in the data before depositing the anonymised data on Zenodo Repository assigned with a persistent identifier (DOI).

### Statistical methods and analysis

#### Sample size

The target study population are people with post-COVID-19 condition living in Switzerland. To calculate the sample size of this study, we used data from two previous studies. In the feasibility study with persons with long COVID-related fatigue, the mean difference of the primary outcome (self-efficacy in performing energy conservation strategies) at T2 (post-intervention) was 1.9 (95% CI: 2.89 to 0.90).^23^ We hypothesised, therefore, a difference of 1.5 points at T2 and conservative assumption of a SD of 2.2 points.^38^ Including a follow-up rate of 24% at T2, the estimated sample size to detect a difference of 1.5 points with 90% power (0.05 alpha) is 122 persons. Therefore, we aim at a total of 122 persons included in the study (eg, 61 and CG: 61).

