Lesson 7	Individual or group face-to-face/ 45 or 90 min.		Apply in daily life	
Lesson 8 (Booster)	Individual or group, approx. 8 weeks after lesson 7		Review and reinforce	

At the University Hospital Bern (INSEL) and Clinic for Neurorehabilitation Basel (REHAB), the intervention starts with an individual lesson (45 min), whereas at University Hospital Zürich (USZ), the first lesson is already delivered in groups (90 min). With a frequency of one lesson per week, lessons 2–7 are provided (duration 90 min, appr. five participants). EME finishes with a group lesson, approximately 8 weeks after lesson 7. REHAB provides lessons 7 and 8 as individual lessons of 45 min. The EME-leading OTs use the treatment manual, which describes in detail the tasks of each lesson. All EME participants receive the workbook, which contains relevant information on the topics covered in each session, including worksheets and space for personal notes plus self-training tasks.

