Outcomes	Impact of fatigue on physical, mental and social activities of daily routines measured by the Modified Fatigue Impact Scale Self-efficacy in performing energy management strategies measured using the Self-Efficacy for Performing Energy Conservation Strategies Assessment Perceived competency to perform 21 daily tasks measured by the Occupational Self-Assessment Health-related quality of life using the Short-Form 12 Item Health-Related Quality of Life Survey Description of the stable use of energy management strategies in daily life using the Behavioural Changes in Energy Management Survey Cost-effectiveness profile of the EME intervention plus the standard care vs standard care only: a self-reported questionnaire about disease-related and productivity costs
Interventions to be compared	Standard care: any interventions tailored to the personalised needs and goals of persons with long COVID Standard care plus occupatinal therapist-EME-group participation
Causal contrast	Per-protocol effect
Analysis plan	Each participant in the EG will be matched (1:1 ratio) to a participant in the CG by applying the optimal matching method using propensity score as a distance measure Outcomes will be analysed using an adjusted repeated measures mixed-effects linear regression model Cost-effectiveness by performing an economic evaluation

To emulate random assignment, each participant in the EG will be prospectively matched to a participant in the register according to their baseline sociodemographic characteristics (sex and age) and clinical history of long-COVID-related fatigue. We will choose 1:1 optimal matching using PS as a distance measure. We will employ a prospective matched design to compare outcomes between the experimental group and CGs. This ensures that CG participants are carefully selected in real time, concurrently with the enrolment of EG participants, to maximise group comparability and reduce confounding. For every 15 participants who are enrolled in the EG, we will prospectively match one CG participant to each EG participant. Optimal matching minimises the overall sum of pair-wise distances between treatment subjects and matched control subjects and is recommended when matching for the purpose of selecting well-matched controls for follow-up (eg, when the outcome values are not yet available).^39^

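### The 24% in the sample-size statement is a loss rate mislabelled as follow-up; separately, 122 makes no allowance for teaching the EME arm in peer groups, so the stated 90% power is optimistic

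*Protocol article*

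**What the plan says.** The Sample size section of the protocol article sets out the calculation for the self-efficacy score at T2. The target is given by "We hypothesised, therefore, a difference of 1.5 points at T2", with a "conservative assumption of a SD of 2.2 points". Attrition and the result come in one sentence, "Including a follow-up rate of 24% at T2, the estimated sample size to detect a difference of 1.5 points with 90% power (0.05 alpha"), which gives 122 persons, split 61 and 61. The section mentions no ICC or design effect.

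The Interventions section describes how EME is delivered. Table 1 gives groups of 3 to 7, and the text below it says "lessons 2–7 are provided (duration 90 min, appr. five participants"). Table 1 also lists sharing of experience and social support among the techniques applied, so contact between group members is part of the treatment. Controls receive standard care without an EME group.

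For the analysis, Table 4 states: "Outcomes will be analysed using an adjusted repeated measures mixed-effects linear regression model". Neither the table nor the Statistical analysis text lists the random effects.

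**The concern.** The attrition phrase contradicts the result it is meant to explain. A reader checking the sample size cannot tell from the wording whether 24% or 76% are expected to reach T2.

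The second matter is one of substance. People who learn in the same small group, with the same therapist and with each other's help, tend to have correlated outcomes. Controls have no such group. Positive correlation in one arm inflates the variance of the T2 difference. A calculation for independent observations then promises more power than the design delivers, and a model without a group term gives intervals that are too narrow.

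**Working it through.** **Inputs from the Sample size section:** difference 1.5, SD 2.2, power 90%, alpha 0.05 (two-sided is assumed because it reproduces the total), 24% at T2, 61 per arm. **From the Interventions section:** group size m about 5, range 3 to 7, EME arm only. **Assumed, not in the documents:** ICC from 0.02 to 0.10.

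**1. Reproducing 122.** n = 2(1.96 + 1.2816)² × (2.2/1.5)² = 45.2, so 46 per arm. With 24% lost, 46/0.76 = 60.5, so 61 per arm and 122 in total, which matches exactly. If only 24% were retained, 46/0.24 = 191.7, so 192 per arm and 384 in total, which does not match. The 24% was therefore used as loss.

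**2. Room for a design effect.** The only slack is rounding: 45.2 to 46, and 60.5 to 61. That is less than one person per arm at each step, so 122 is the independent-observations size. At 46 completers per arm, power is 90.5% by the normal approximation and 89.9% by the t-test.

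**3. One-arm clustering.** The variance in the EME arm is multiplied by DE = 1 + (m − 1) × ICC and that of the controls by 1. The variance of the difference is therefore multiplied by (1 + DE)/2.

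Example with m = 5 and ICC 0.05:
- DE = 1 + 4 × 0.05 = 1.20, and the factor is (1 + 1.20)/2 = 1.10.
- The SE ratio is √1.10 = 1.049.
- The independence SE is 2.2 × √(2/46) = 0.459, which becomes 0.481.
- 1.5/0.481 = 3.12. Power is 87.7% (normal) or 87.0% (t-test).
- Small-sample degrees of freedom (Satterthwaite) with 46/5 = 9.2 groups: (1 + 1.20)² / (1.20²/8.2 + 1/45) = 24.5. Power is then 84.9%.

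**4. Analysed group size.** Groups of five applied to 46 completers may be on the high side. If 61 people form about 12 groups (61/5 = 12.2) and 46 complete, the analysed size is 46/12, about 3.8. Both cases are shown.

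**5. Type I error if no group term is fitted:** 2 × [1 − Φ(1.96 / SE ratio)]. For the example, 1.96/1.049 gives 6.2%.

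| m | ICC | Variance factor | SE ratio | Power, t-test | Power, small-sample df | Type I error without group term |
|---|---|---|---|---|---|---|
| 5 | 0.02 | 1.04 | 1.02 | 88.7% | 87.0% | 5.5% |
| 5 | 0.05 | 1.10 | 1.05 | 87.0% | 84.9% | 6.2% |
| 5 | 0.10 | 1.20 | 1.10 | 84.0% | 81.4% | 7.4% |
| 3.8 | 0.02 | 1.03 | 1.01 | 89.1% | 88.0% | 5.3% |
| 3.8 | 0.05 | 1.07 | 1.03 | 87.8% | 86.6% | 5.8% |
| 3.8 | 0.10 | 1.14 | 1.07 | 85.8% | 84.3% | 6.6% |

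Part of the drop in the small-sample column is the cost of estimating from few groups. Even at ICC 0, those degrees of freedom give 88.4% (m = 5) or 88.9% (m = 3.8).

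**The case against.** The case against making much of this has four parts.

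- **The 24% is only a label.** This stands. A reader might infer from the literal wording that about 15 per arm (61 × 0.24 = 14.6) will be analysed, with power near 44%. The documents do not support that, since their own total requires 24% loss. No such design was planned.
- **The analysis may already handle the groups.** This also stands. A reader might infer that the model has person-level terms only and that the T2 test therefore exceeds 5%. The article names a mixed model without listing its random effects, and that detail may sit in an analysis plan not shown. The standard-error and type I error consequences are therefore conditional. The sample-size point is not, because that calculation is fixed in the article and is reproduced exactly without a design effect.
- **The ICC is unknown and the loss may be small.** True. At ICC 0.02 the t-test power falls by only about one point, and analysed groups may be smaller still because members must consent individually.
- **Baseline adjustment could restore the power.** Possibly. With an assumed baseline correlation of 0.4, the residual variance is multiplied by 1 − 0.16 = 0.84. At m = 5 and ICC 0.10 the net factor is 1.20 × 0.84 = 1.008, so power is about 90% before the degrees-of-freedom correction. The Sample size section claims no such gain, however, and adjusting for baseline is no substitute for a group term.

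**Conclusion.** The point holds in two parts of unequal weight. The attrition label is wrong and needs an editorial correction only; 122 and its arithmetic are unaffected.

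The 90% power is optimistic under the plan's own calculation for any material positive ICC. The shortfall is modest: a few points at the assumed ICCs, and up to about nine at ICC 0.10 with groups of five and small-sample degrees of freedom. These figures rest on an assumed ICC, 46 completers per arm, 3.8 to 5 analysed per group, and no credit for baseline adjustment. Whether the final analysis will actually fall short of 90% cannot be settled from the documents. The shortfall does not by itself call for a larger trial.

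**What to change.** - Reword the attrition phrase as a loss to follow-up of 24% (76% retained).
- Keep 122, and state the power as conditional on an assumed ICC: about 81% to 88% for ICC 0.02 to 0.10 with small-sample degrees of freedom, before any gain from baseline adjustment.
- Record which EME group each EME participant attended.
- Specify a partially nested mixed model: a random effect for EME group in the EME arm only, each control treated as a cluster of one, small-sample degrees of freedom, and the person-level term for repeated measures. If an analysis plan already contains this, a cross-reference is enough.

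The cost is one identifier, one variance component, slightly wider intervals and a slightly less favourable power statement. The article places the start of data analysis at the end of 2025, after the last T3 assessment, so the plan's own timetable leaves room to settle this before outcomes are analysed.

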#### Statistical analysis

We will emulate a prospective interventional study that makes causal inferences on the effectiveness of adding EME to the standard care using a target trial emulation approach (see table 4).^28 29^

**Table 4 T4:** Target trial protocol components

Protocol component	Emulated target trial
Eligibility criteria	Inclusion criteria: Living in Switzerland Age ≥18 years Diagnosed with post-COVID-19 condition Confirmed experience of living with fatigue (MFIS, cut-off >38)^47^ No major depression (Beck depression inventory (BDI)-FS cut-off <8)^48^ No major cognitive impairments (Mini-Mental State Examination (MMSE) cut-off of ≥26 for the experimental group and MMSE-telephone version for the control group (CG), cut-off≥21)^49 50^ Ability to understand and speak German, French or Italian and to fulfil the assessments Ability to give informed consent as documented by signature Exclusion criteria: Participation in an energy management education (EME) group or starting it during the study duration (only CG) History of severe neurological diseases (eg, stroke, MS and Morbus Parkinson’s disease) or mental health disorders (eg, schizophrenia, major depression, schizophrenia or dementia) Inability to follow the procedures of the study, for example, due to language problems, psychological disorders, dementia, etc.
Recruitment	Experimental group (eg,) participants at three study sites (INSEL, USZ, REHB) consecutive ongoing from mid-July 2024 up to the required number of 61 participants; maximum until end of 2025 A register for potential CG participants disseminated through the national patient organisations and specified healthcare providers
Follow-up	24 weeks after enrolment in the study
Outcomes	Impact of fatigue on physical, mental and social activities of daily routines measured by the Modified Fatigue Impact Scale Self-efficacy in performing energy management strategies measured using the Self-Efficacy for Performing Energy Conservation Strategies Assessment Perceived competency to perform 21 daily tasks measured by the Occupational Self-Assessment Health-related quality of life using the Short-Form 12 Item Health-Related Quality of Life Survey Description of the stable use of energy management strategies in daily life using the Behavioural Changes in Energy Management Survey Cost-effectiveness profile of the EME intervention plus the standard care vs standard care only: a self-reported questionnaire about disease-related and productivity costs
Interventions to be compared	Standard care: any interventions tailored to the personalised needs and goals of persons with long COVID Standard care plus occupatinal therapist-EME-group participation
Causal contrast	Per-protocol effect
Analysis plan	Each participant in the EG will be matched (1:1 ratio) to a participant in the CG by applying the optimal matching method using propensity score as a distance measure Outcomes will be analysed using an adjusted repeated measures mixed-effects linear regression model Cost-effectiveness by performing an economic evaluation

To emulate random assignment, each participant in the EG will be prospectively matched to a participant in the register according to their baseline sociodemographic characteristics (sex and age) and clinical history of long-COVID-related fatigue. We will choose 1:1 optimal matching using PS as a distance measure. We will employ a prospective matched design to compare outcomes between the experimental group and CGs. This ensures that CG participants are carefully selected in real time, concurrently with the enrolment of EG participants, to maximise group comparability and reduce confounding. For every 15 participants who are enrolled in the EG, we will prospectively match one CG participant to each EG participant. Optimal matching minimises the overall sum of pair-wise distances between treatment subjects and matched control subjects and is recommended when matching for the purpose of selecting well-matched controls for follow-up (eg, when the outcome values are not yet available).^39^

Descriptive statistics will be used for all outcome measures at each measurement time to summarise results. To ensure that PS matching adequately balances measured confounders, we will carefully assess and report standardised differences between treatment groups before and after matching.^40^ Standardised differences are widely used because they are unaffected by sample size and provide a consistent measure of imbalance. A standardised difference of less than 10% (0.1 in absolute value) will be considered indicative of a clinically relevant balance between groups. Variables with standardised differences of greater than 10% will be flagged for potential residual confounding and addressed in sensitivity analyses.

Our causal contrast of interest will be the per-protocol effect, so to analyse the effect of adding EME to the standard care on the dependent continuous variables for both primary and secondary outcomes, an adjusted repeated measures mixed-effects linear regression model will be used. In addition to the covariates already included in the matching phase, we are aiming to include additional potential covariates related to the clinical history of long-COVID (eg, fatigue intensity, fatigue impact) and socio-demographic data (eg, education, occupation status).

Using PS matching combined with regression methods is a robust approach to account for measured confounding. However, this approach does not address unmeasured confounding, which could bias the results. To acknowledge this limitation and mitigate its impact, we will perform a sensitivity analysis to evaluate the robustness of your findings to potential unmeasured confounding. We will perform a simulated bias analysis to estimate the potential impact of unmeasured confounding. We will specify plausible distributions for an unmeasured confounder and assess its potential effect on the treatment-outcome relationship.^41^ In addition, we plan to conduct an E-value analysis for assessing whether our results are likely robust even in the presence of unmeasured confounders.^42^ The E-value quantifies the minimum strength of association that an unmeasured confounder would need to have with both the treatment and the outcome (beyond measured confounders) to explain away the observed treatment effect.^43^

Cost-effectiveness of EME intervention against the standard care only will be evaluated by performing an economic evaluation, using the direct costs of delivering the intervention, disease-related and productivity as the cost input and various outcomes as health effects. A probabilistic sensitivity analysis will be performed to consider the uncertainty in the various input parameters and their effects on the decision-making process. After the maximal efforts have been employed to minimise the presence missing data, we will employ, beyond the default complete case analysis, a multiple imputation approach to assess the robustness of results.^44^ Statistical analysis will be performed using Stata (Stata, College Station, Texas, USA) and R (R Core Team (2023) R: A Language and Environment for Statistical Computing. R Foundation for Statistical Computing, Vienna, Austria; <https://www.R-project.org/>).

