## Methods and analysis

### Project status

The recruitment at the three intervention group sites and for the control group (CG) register started in July 2024. The time between registration in the study and matching for the CG depends on the recruitment rate of the EME participants. The first matching of 15 participants of the experimental group with 15 participants out of the CG register was performed in December 2024. Study participation lasts for each study participant approximately 24 weeks; therefore, data collection was not finished with any participant before submission of this article. The recruitment will be finished during late summer/early autumn 2025, and data collection will be finished at approximately the end of 2025.

Data analysis will begin at the end of 2025 after the last participant has completed T3. The total duration of the research project is 42 months.

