### Setting and recruiting

*Experimental group (EME, outpatient version 2023, plus standard care):* persons with long COVID-related fatigue following EME (revised edition 2023) in an outpatient setting at USZ, INSEL or REHAB, as part of their clinical routine and standard care, will be informed about this ongoing research and will be kindly asked if they are willing to participate in this project. If individuals agree, have signed the consent form and meet the inclusion/exclusion criteria checked by the study therapist on site, they will be included in the experimental group (EG). In these three public institutions, a group of trained OTs leads continuously EME groups and has received up-to-date training for the EME version 2023 in Spring 2024.

*CG (standard care*): a register of potential CG participants will be created through a contact with the Altea Network for Long COVID Association (ALTEA) and the patient organisation Long Covid Switzerland (LCS), both of which are partners in the study project and have been involved since the design phase. Using the contacts of ALTEA, LCS and specialised healthcare providers, information about the study will be disseminated, allowing interested persons to register themselves through a public link or QR code and to participate in a first online survey. Registration for the study has been open since 15 July 2024 and will remain open until summer 2025. Thereafter, based on the sociodemographic characteristics and clinical history of COVID-19, the CG participants will be selected from the register by their propensity score (PS) and matched with EG participants. Subsequently, the selected persons from the CG will be screened for eligibility, asked for their informed consent and included in the study.

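### Matching in batches of 15 starts each control's follow-up weeks to months after its partner's, so the stated pair-level concurrency is not delivered and calendar time is not among the named covariates

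*Protocol article*

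**What the plan says.** In the protocol article, Statistical analysis, the text after Table 4 says the design ensures that "CG participants are carefully selected in real time, concurrently with the enrolment of EG participants". It gives this as the means of making the groups comparable and reducing confounding. The next sentence sets the trigger: "For every 15 participants who are enrolled in the EG, we will prospectively match one CG participant to each EG participant".

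Project status gives the dates. "The recruitment at the three intervention group sites and for the control group (CG) register started in July 2024", and "The first matching of 15 participants of the experimental group with 15 participants out of the CG register was performed in December 2024". Table 4 describes EG recruitment as "consecutive ongoing from mid-July 2024 up to the required number of 61 participants; maximum until end of 2025". The expected end is earlier: "The recruitment will be finished during late summer/early autumn 2025".

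On the control side, Setting and recruiting puts further steps after the match: "Subsequently, the selected persons from the CG will be screened for eligibility, asked for their informed consent and included in the study". Table 2 places matching, eligibility check and consent at week -2 and the control's T0 at week 0. Table 3 places EG consent, sociodemographic data and clinical history at T0, when the lessons begin.

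The article acknowledges one delay: "The time between registration in the study and matching for the CG depends on the recruitment rate of the EME participants". That is the wait in the register, not the offset between the follow-up windows of a pair.

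**The concern.** If matching waits for a batch of 15, the first people in the batch are well into follow-up, or past T2 at week 14, before their controls complete T0. The offset always runs the same way, because no control can start before its partner.

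The study claims causal inference by target trial emulation, in which both arms would share a time zero. Whatever changes with calendar time (circulating infection, available long COVID care, work conditions) can then differ systematically between arms at T2 and in the productivity costs. The named matching variables are sex, age and clinical history. The example covariates are fatigue intensity, fatigue impact, education and occupation status. None of these captures calendar time.

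**Working it through.** **Order of events.** EG matching data exist only from the EG participant's T0 (Table 3). Matching needs 15 such participants. The control's T0 follows matching by about 2 weeks (Table 2). Hence, for the i-th EG member of a batch that takes B weeks to fill under even accrual:

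lag(i) = B − iB/15 + 2 weeks

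The last member (i = 15) has lag 2. The first has 14B/15 + 2. The mean is 7B/15 + 2.

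**First batch.** From 15 July 2024 to 1 December is 139 days (19.9 weeks), and to 31 December 169 days (24.1 weeks). Take B = 20 to 24.

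| | B = 20 | B = 24 |
|---|---|---|
| Mean lag | 7×20/15 + 2 = 11.3 weeks | 7×24/15 + 2 = 13.2 weeks |
| Longest lag | 14×20/15 + 2 = 20.7 weeks | 14×24/15 + 2 = 24.4 weeks |
| Pairs with lag ≥ 14 weeks | 6 of 15 | 7 of 15 |

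In the last row, the EG partner's T0–T2 window has closed by the time the control's opens.

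**Later start.** The article gives no individual T0 dates. If the first T0s fell only on 1 September and the batch filled by 15 December, B = 15: mean 7×15/15 + 2 = 9 weeks, longest 14×15/15 + 2 = 16 weeks. Tighter clustering near December would shorten this further, towards the 2-week minimum.

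**Whole recruitment.** From 15 July 2024 to 31 August or 15 October 2025 (taken as late summer to early autumn) is 58.9 to 65.3 weeks. A batch of 15 out of 61 then takes 58.9×15/61 = 14.5 to 65.3×15/61 = 16.1 weeks. The mean lag is 7×14.5/15 + 2 = 8.8 to 7×16.1/15 + 2 = 9.5 weeks, and the longest about 15.5 to 17 weeks. At the Table 4 limit (end of 2025, 76.3 weeks) the mean is about 10.8 weeks.

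**Does a seasonal effect survive across batches?** Let an annual sinusoid of amplitude A act on the outcome, and take the worst phase. The net shift is A times the modulus of the difference between the arms' mean values of exp(iωt), with ω = 2π/52 per week. For change from T0 to T2 this is multiplied by 2 sin(7ω) ≈ 1.49.

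- First batch alone: about 1.2A on level, and 1.2 × 1.49 ≈ 1.8A on change.
- All 61 pairs, recruitment of 59 to 65 weeks: at most about 0.2A on level and 0.2 × 1.49 ≈ 0.3A on change.

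Recruitment spans slightly more than a year, so the sign reverses between batches and most of the effect cancels.

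**Cost of adjustment.** Under the same accrual, arm and T0 date correlate at only about 0.27. A linear date term inflates the variance of the treatment effect by about 1/(1 − 0.27²) = 1.08, or about 4% on the standard error.

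**The case against.** The strongest reply is that the batch rule is disclosed in the very next sentence. In context, prospective and concurrent selection may mean only that controls are chosen before outcomes exist and are followed within the same overall study period. That stands in part: these controls are lagged, not historical, and the Selection bias section rightly says that no post-baseline EG information is used to choose them. That safeguard deals with selection, however, not with timing.

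A reader might go further and infer that the primary effect is confounded with season. The document does not support this. It gives no seasonal effect on self-efficacy or fatigue impact, and a regular annual effect largely cancels across batches. A secular trend, an epidemic wave or a change in available care would not cancel in that way. Even so, the T0 measurement in the repeated-measures model can absorb whatever shifts T0 and T2 equally.

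A reader might also infer, from 61 = 4×15 + 1, that the last EG participant goes unmatched. Table 4 says each EG participant is matched 1:1, and the sample size section sets 61 per group, so 15 is a batch size and nothing more.

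Finally, the additional covariates are given as examples, and an analysis plan not shown here may name calendar time. Its absence from the article is therefore not the finding on its own. The finding is a stated design property that the article's own schedule contradicts. The planned E-value and simulated bias analyses address unmeasured confounders, whereas the T0 date can be measured and modelled directly.

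**Conclusion.** The point holds at the level of the pair. The batch trigger and the order of steps in Tables 2 and 3 put every control's T0 at least about 2 weeks after its partner's. With the July-to-December 2024 interval, the lag may reach several months for the earliest EG participants. The means of about 11 to 13 weeks in the first batch and about 9 weeks overall rest on even accrual from mid-July 2024, on matching as soon as a batch fills, and on the 2-week gap in Table 2. Clustered or later T0s would shorten them.

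Neither the size nor the direction of any resulting bias can be computed from the document. The sample size of 122 is unaffected. This is worth correcting because the remedy is nearly free and the article presents concurrency as already secured. It does not invalidate the design.

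**What to change.** 1. Add the calendar date of T0 (month or season) to the adjusted mixed model for all pairs, including those matched in December 2024. The cost is a few degrees of freedom and a slight loss of precision.
2. Report the distribution of within-pair T0 differences in days.
3. Add a sensitivity analysis limited to pairs with close T0 dates, for example within about 6 weeks. Under even accrual of roughly one EG participant per week, only the last 4 or 5 of each 15 would qualify. That is 16 to 20 pairs from four batches plus the 61st, so about 17 to 21 of 61. It is supportive only, and its width should be set before outcomes are examined.
4. Replace the claim of real-time, concurrent selection with a statement of the batch procedure and the observed lag.

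Smaller matching batches, for instance at each EME group start (3 to 7 people, Table 1), would shorten the lag for the remaining participants. They are optional: optimal matching over fewer EG members may give poorer matches, and the cycle of matching, screening and consent would run more often.
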